### Statistical Analysis

All data will be analyzed on an intention to treat basis. The primary efficacy analysis will be to compare the change in the HbA1c from baseline to 12 months in the intervention and control groups. For all primary and secondary outcome variables, we will analyze differences between groups by using mixed models in SPSS 13.5 to allow for clustering. We will add all relevant baseline characteristics at patient level (age, sex, educational level, cardiovascular risk, clinical vascular disease, medication for primary and secondary prevention) as well as at cluster level if applicable as covariates to the models. Results of two-sided tests between study arms will be regarded significant at p < 0.05.

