## Methods/Design

### Study Design

The study is performed as a cluster-randomized controlled trial of a complex intervention with an observation time of one year. Randomization-clusters are the districts of the province of Salzburg because randomization is neither feasible at the level of the patient nor at the level of the GP. Randomization at the level of the patient leads to the problem that a single GP would have to treat some patients according to usual care and others according to the DMP which is hardly possible because of "contamination" effects. Also, randomization at the level of the GP appears not to be advisable, because this would lead to contamination effects especially in rural areas, where neighbouring GPs have overlapping patient groups. Patients knowing one another and belonging one to the intervention and the other to the control group, may even switch their physician.

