#### Randomisation

Randomisation takes place at the level of the districts after completion of physician recruitment. The city of Salzburg as the only urban region of the province is divided into two study districts (one being to the right, the other to the left of the Salzach, the river that divides the city in nearly two halves). To assure even distribution of the districts regarding population characteristics and size the districts are randomized as matched pairs. Salzburg city to the right of the Salzach is matched with the city left of the Salzach, the district Pongau is matched with Pinzgau and Lungau (mostly mountainous regions with remote villages), and the district Flachgau is matched with Tennengau (both adjacent to Salzburg city with partially suburban and partially agricultural regions, more densely populated than the mountain districts). The randomization process is performed under the supervision of a committee comprising representatives of Paracelsus University, the Austrian public health insurance, the Working-group for Preventive Medicine, Salzburg (AVOS) and the healthcare department of the government of the province.

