Another drawback of our RCT is the possibility of bias due to the cluster randomization and the lack of blinding. Of course, blinding of a complex intervention is not possible. Thus physicians in the intervention group may recruit different patients than those in the control group. Adjustments for these differences using multivariate testing will help to avoid and overcome this bias. As mentioned above, we chose randomization at the level of the district to avoid contamination. Nonetheless we prefer to perform the evaluation at the patient level because the benefit regarding clinical outcome is most important to the individual patient. The drawback of this approach is that cluster effects may be underestimated. Specific analysis of these effects and inclusion in the evaluation models will help to avoid this bias.

Another possible weakness may be the sample of participating physicians. Although the overall participation rate was quite high, the sample may not be representative for all GPs and internists in the country. It rather represents a subgroup more open to innovation and highly motivated to improve patient care. Nevertheless we feel that the sample may be quite representative for the physicians that will finally apply the DMP in everyday practice.

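### The analysis does not say that the treatment effect is tested against variation between the six randomised units; a model clustering only on surgery could exceed the nominal 5% error

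*Protocol article*

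**What the plan says.** Study Design in the protocol article makes the district the unit of allocation and rejects allocation by patient or by practitioner: "Randomization-clusters are the districts of the province of Salzburg because randomization is neither feasible at the level of the patient nor at the level of" (sentence cut here). The Randomisation section adds: "To assure even distribution of the districts regarding population characteristics and size the districts are randomized as matched pairs". The pairs are the two halves of Salzburg city, Pongau against Pinzgau with Lungau, and Flachgau against Tennengau. That is six allocation units formed from seven named areas. Current status of the study confirms three units per arm.

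The sample size section uses an ICC of 0.05 and an average cluster size of 20.

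The Statistical Analysis section states that for all primary and secondary outcomes "we will analyze differences between groups by using mixed models in SPSS 13.5 to allow for clustering". Baseline characteristics enter at patient level "as well as at cluster level if applicable as covariates to the models". The decision rule is "Results of two-sided tests between study arms will be regarded significant at p < 0.05".

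The Discussion returns to the level of analysis: "Nonetheless we prefer to perform the evaluation at the patient level". It concedes: "The drawback of this approach is that cluster effects may be underestimated". It then offers a remedy: "Specific analysis of these effects and inclusion in the evaluation models will help to avoid this bias". Neither section names the level of the cluster effect, a pair term or the degrees of freedom.

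**The concern.** Treatment differs only between the six allocation units. The standard error of the treatment effect must therefore include variation between those units, and the reference distribution must reflect how few there are.

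The article uses the word cluster in two senses. Where it describes allocation, a cluster is a district. Where it puts a number on a cluster, the cluster is the size of a surgery. An analysis written to match the sample size section would put the random effect at surgery. Differences between districts, for example in case mix or access to care, would then be left out of the standard error and could be read as an effect of the programme.

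The same model and the same p < 0.05 rule apply to the primary and all secondary outcomes, so the consequence is not confined to HbA1c.

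**Working it through.** **Inputs from the article.** SD of HbA1c change 2%; difference 0.5%; two-sided alpha 0.05; power 80%; ICC 0.05; cluster size 20; drop-out 20%; 1494 patients recruited by 96 physicians; six allocation units.

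**The plan's own figure.** A two-sample t-test for 0.25 SD needs 252 per arm. The design effect is 1 + 19 × 0.05 = 1.95. Then 252 × 1.95 = 491.4, rounded up to 492 per arm (984), and 492 / 0.8 = 615 per arm, 1230 in total. This reproduces exactly.

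**Which cluster has size 20?** Patients per recruiting physician: 1494 / 96 = 15.6. Patients per allocation unit: 1494 / 6 = 249, or 1230 / 6 = 205 as planned. The figure of 20 fits a surgery.

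**Type I error if surgery is the only random effect.** Assumptions: 3 units per arm, 16 surgeries per unit, 12 completers per surgery, balanced; total within-surgery ICC 0.05, of which the district share d is varied; a fraction s of the district variance lies between pairs and so cancels in the comparison. The article gives neither d nor s. In units of the SD:

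- Variance assumed by a surgery-level model: 2 × (0.05 + 0.95/12) / 48 = 0.00538. The SE is 0.0734 SD, or 0.147% HbA1c.
- True variance: 2 × [d(1 − s)/3 + (0.05 − d)/48 + 0.95/576].

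Example with d = 0.01 and s = 0: 2 × (0.003333 + 0.000833 + 0.001649) = 0.01163. The true SE is 0.1079 SD, or 0.216% HbA1c. The effective critical value is 1.96 × 0.147/0.216 = 1.33, which gives an error of about 18%. With s = 0.5 the true SE is 0.182% and the error about 11%.

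Simulation (20,000 null trials per scenario, t-test on surgery means, 94 df) agrees closely:

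| District ICC (assumed) | Half of district variance between pairs | None between pairs |
|---|---|---|
| 0 | 5% | 5% |
| 0.0025 | 6–7% | 8% |
| 0.005 | 8% | 12% |
| 0.01 | 12% | 18–19% |
| 0.02 | 18–19% | 29% |

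**Other readings of the same sentence** (no variance between pairs, district ICC from 0 to 0.05). A district random intercept with a normal reference gives 3.9% to 12.2%. A district random intercept with about 4 df gives 3.1% to 5.3%.

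**Tests based on the randomised units.** With no variance between pairs, a t-test on the six unit means (4 df) holds about 5%. It becomes conservative when matching works: about 3% at district ICC 0.01 with half of the variance between pairs. A paired t-test (2 df) holds about 5% in every scenario.

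**Power of unit-level inference.** For 0.25 SD with 984 completers (164 per unit, 16 surgeries per unit), the variance of the difference is (2/3) × [d + (0.05 − d)/16 + 0.95/164], assuming no variance between pairs. From the noncentral t distribution:

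| District ICC (assumed) | 4 df | 2 df |
|---|---|---|
| 0 | 68% | 43% |
| 0.005 | 51% | 32% |
| 0.01 | 41% | 26% |

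If matching removes half of the district variance, the 2-df power at district ICC 0.01 is about 33% instead of 26%.

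**The case against.** The strongest reply is that the article never says surgery is the only random effect. It defines its clusters as districts, promises a mixed model that allows for clustering, and follows its admission of possible underestimation with "Specific analysis of these effects and inclusion in the evaluation models will help to avoid this bias". On that reading, clustering means districts, and the random-effect structure and degrees of freedom are details that an article leaves to an analysis plan. Patient-level modelling with proper cluster effects is legitimate, so the stated preference for it is not an error in itself. Matching also removes some district variation, and the district ICC is unknown.

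Much of this stands. A reader might infer that the planned test has a type I error of 10–30%, or that patient-level evaluation means ignoring allocation. The documents support neither. A district random effect is not excluded and, with about 4 df, would be close to nominal. The 10–30% range needs a surgery-only model, matching that removes nothing and a district ICC of roughly 0.004 to 0.02. Carrying the article's ICC of 0.05 over to districts gives about 48%, but that assigns all within-surgery correlation to the district, which the article does not say.

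The reply does not dispose of the ambiguity. The promise in the Discussion fixes neither level nor reference distribution, and the only quantified cluster is not the one that was randomised. A later plan could follow either sense and claim consistency with this text. Adding a district effect without small-sample degrees of freedom can also be anti-conservative.

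**Conclusion.** The concern holds as a conditional one. The article allocates six units in three pairs, quantifies only a surgery-sized cluster, and does not tie the test to the randomised units. If surgery is the only cluster level, the error at nominal 5% is about 8–12%, 12–19% and 19–29% at district ICCs of 0.005, 0.01 and 0.02. It is about 5% if districts do not differ.

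These figures rest on assumed district ICCs, an assumed benefit of matching between none and one half, and a balanced layout. The real arms are unequal (654 and 840 patients). That the level of inference is left open does not depend on any of these assumptions. It should be settled before the 12-month data are analysed; at the time of the article, baseline data were still being processed.

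**What to change.** In Statistical Analysis:

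- Name the allocation unit as the level of inference, with a random intercept for the unit and surgery nested within it.
- Use between-unit small-sample degrees of freedom, kept even if the unit variance is estimated as zero: at most 4 if pairs are ignored (conservative if matching works), or 2 if pairs are modelled. State the choice in advance.
- Do not add covariates measured at allocation-unit level, since each would use up one of these few degrees of freedom. Patient-level and surgery-level covariates can stay.
- Label any surgery-only model a sensitivity analysis.

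In the Discussion, say that patient-level modelling still uses inference based on the allocation units.

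In the sample size section, state that the cluster of 20 is a surgery, and restate power. The 80% no longer holds: with 984 completers it is about 68%, 51% and 41% with 4 df, or 43%, 32% and 26% with 2 df, at district ICCs of 0, 0.005 and 0.01.

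The change needs only new wording and one more model level, but its statistical cost is real: wider intervals and much lower power. Randomisation and recruitment are complete, so adding units cannot repair this. An exact permutation test is no way out either: with three pairs its smallest two-sided p-value is 2/8 = 0.25.

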**Methods/Design:**

The study is open for participation to all GPs and internists in the province of Salzburg. Physicians are randomized before recruitment of patients with the districts of Salzburg as clusters of randomisation. A total of over 1200 patients with type 2 diabetes will then be recruited. In the intervention group the DMP is applied for one year. Controls receive usual care. Endpoints are a decrease in HbA1c in the intervention group > 0,5% compared to controls, a higher percentage of patients with required diagnostic measures according to guidelines, improved cardiovascular risk profile and higher quality of life scores within one year.

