#### Recruitment of patients

All patients (> 18 years) with type 2 diabetes that fulfil the WHO/ADA-criteria for diabetes diagnosis are eligible to participate in the study. The physicians are encouraged to continuously recruit all patients with type 2 diabetes that enter the surgery during the recruitment period (from July 1^st ^to October 31^st ^of 2007). All patients willing to participate are included in the study after informed consent according to the declaration of Helsinki.

Exclusion criteria are dementia/psychiatric illness with inability to participate or to give informed consent, or known major consuming illness (i.e. advanced cancer).

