### Documentation and Monitoring

#### Baseline-Examination

At inclusion the following parameters are examined and recorded:

**• Laboratory**: Fasting and postprandial blood glucose, HbA1c, cholesterol, triglycerides, HDL-cholesterol

**• Anthropometric measurements**: Height and body weight, systolic and diastolic blood pressure

**• Case Report Form**: In the intervention group the DMP documentation form is used. To avoid bias, a simplified case report form is used in the control group. Some parameters (i.e. known diabetic complications) will be registered at the end of the study, see below).

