### Current status of the study

Recruitment of the surgeries took place from April 18^th ^to June 5^th ^2007. 98 Physicians declared themselves willing to participate in the study (88 GPs and 10 specialists in internal medicine) yielding a participation rate of 35.6% of all physicians eligible. Randomization took place on June 5^th ^2007. Salzburg city to the left of the Salzach river and the districts Pinzgau, Lungau and Tennengau were allocated to the intervention group (48 physicians), Salzburg city to the right of the Salzach river and the districts Flachgau and Pongau form the control group (50 physicians). The physicians of the intervention group received their DMP-training-courses in June and July of 2007. Recruitment of patients took place from July 1^st ^to October 31^st ^2007. Two surgeries dropped out and didn't recruit any patients. 1494 patients entered the study (654 in the intervention group and 840 in the control group). Baseline data are currently being processed.

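### The adjustment relied on to offset selective recruitment does not name diabetes duration or baseline HbA1c and leaves glucose-lowering treatment unclear, so unequal disease stage could bias the HbA1c comparison in either direction

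*Protocol article*

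**What the plan says.** Eligibility (Recruitment of patients) is wide: "All patients (> 18 years) with type 2 diabetes that fulfil the WHO/ADA-criteria for diabetes diagnosis are eligible to participate in the study". The exclusions do not touch disease stage: "Exclusion criteria are dementia/psychiatric illness with inability to participate or to give informed consent, or known major consuming illness". Nothing limits time since diagnosis or current treatment.

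Allocation comes first. The abstract states: "Physicians are randomized before recruitment of patients with the districts of Salzburg as clusters of randomisation". Current status of the study dates randomisation to June 5th 2007 and patient recruitment to July 1st through October 31st. On training it says: "The physicians of the intervention group received their DMP-training-courses in June and July of 2007".

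The Discussion accepts that there is no blinding and draws the consequence: "Thus physicians in the intervention group may recruit different patients than those in the control group". Its stated remedy is multivariate adjustment.

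Statistical Analysis commits to adjusting for the relevant patient-level baseline characteristics and lists them in brackets: "age, sex, educational level, cardiovascular risk, clinical vascular disease, medication for primary and secondary prevention". The laboratory items under Baseline-Examination are "Fasting and postprandial blood glucose, HbA1c, cholesterol, triglycerides, HDL-cholesterol". The primary endpoint is the change in HbA1c from baseline to 12 months.

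**The concern.** The endpoint is a one-year change in a measure of glucose control, and the bias the protocol expects is a difference in who gets recruited. An adjustment meant to deal with that should contain the patient features most likely to predict the change. Disease stage is an obvious one: a patient just diagnosed and starting a first treatment can be expected to change differently over a year from a patient treated for many years.

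The listed covariates are demographic and cardiovascular. They do not name time since diagnosis. The only item that might hold glucose-lowering drugs is the preventive medication, which comes straight after cardiovascular risk and vascular disease and reads most naturally as cardiovascular prevention. Baseline HbA1c, which would carry part of the same information, is measured but not named as a covariate.

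If the arms differ in the share of newly diagnosed patients, part of the observed difference in HbA1c change would reflect case mix, and the model as listed would correct for it only indirectly.

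**Working it through.** **Does allocation protect the balance?** Not for patient selection. Districts were randomised on June 5th 2007, intervention physicians were trained in June and July, and patients were enrolled from July 1st. The reported counts are 654 patients for 48 intervention physicians (654/48 = 13.6) and 840 for 50 control physicians (840/50 = 16.8). Recruitment per physician differed, but these counts say nothing about disease stage.

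**The plan's own sample size.** With SD 2, difference 0.5, two-sided 0.05 and 80% power, the calculation gives 252 per arm. Multiplying by D = 1 + 19 × 0.05 = 1.95 gives 491.4, so 492. Dividing by 0.8 gives 615 per arm and 1230 in total. The figures reproduce, and this point does not change them.

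**Size of a possible bias.** Bias = (difference between arms in the share newly diagnosed) × (extra 12-month fall in HbA1c among them). The documents give neither factor. The ranges below are assumptions, and the extra fall is taken before any adjustment for baseline HbA1c.

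To put the bias on the trial's scale, take the protocol's own SD and design effect with 492 analysed per arm: SE = 2 × √(1.95 × (1/492 + 1/492)) = 0.178. With no true effect, the chance of p < 0.05 is Φ(b/SE − 1.96) + Φ(−b/SE − 1.96).

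| Imbalance | Extra fall | Bias b | Share of 0.5 | Chance of p < 0.05 with no true effect |
|---|---|---|---|---|
| 5 points | 1.0 | 0.05 | 10% | 5.9% |
| 5 points | 2.0 | 0.10 | 20% | 8.7% |
| 10 points | 1.0 | 0.10 | 20% | 8.7% |
| 10 points | 1.5 | 0.15 | 30% | 13.4% |
| 10 points | 2.0 | 0.20 | 40% | 20.2% |

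The same bias in the other direction costs power. If the true difference is 0.5 and the bias is 0.10 or 0.20 against the programme, the expected difference is 0.40 or 0.30. The formula then gives 61.3% or 39.2% instead of the planned 80%.

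To produce the whole 0.5 by case mix alone, the imbalance would have to be 0.5/2.0 = 25 points or 0.5/1.0 = 50 points.

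**The case against.** The strongest reply is that the article is condensed. Age, sex, educational level, vascular disease and medication are covariates, yet none appears under Baseline-Examination, so that list is plainly abridged. The DMP form and the simplified control form are not reproduced, and some items are deferred to a further form at the final examination. A reader might infer that duration and glucose-lowering treatment were never collected, so that no adjustment could reach them. The documents do not support that: the items may be on one form or both. This part of the reply stands.

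The bracketed list might also be illustrative, since the sentence promises all relevant characteristics, and the medication item is undefined. This stands only in part. The list is the one place where the adjustment is given content, and duration is absent on any reading of it.

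The recruitment section also encourages physicians to enrol, continuously, every patient with type 2 diabetes who attends. That limits selection by disease stage but does not remove it, and the Discussion itself still expects a difference.

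Two further inferences are tempting. One is that the early fall after diagnosis would pass for a benefit of the programme. Nothing shows which arm would hold more new cases, so the direction is unknown. The other is that the figures above estimate the actual bias. They do not: both factors are assumed, the larger values fit only patients starting first treatment around inclusion, and adjustment for baseline HbA1c would take away part of the effect.

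**Conclusion.** The point holds as a gap in the named adjustment. The protocol expects selective recruitment after open allocation and makes covariate adjustment its safeguard, but the covariates it names omit diabetes duration and baseline HbA1c and leave glucose-lowering treatment ambiguous. With no limit on duration at entry, unequal disease stage could bias the primary comparison in either direction.

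Under the stated assumptions (5 to 10 point imbalance, extra fall of 1 to 2) the bias is 0.05 to 0.20 HbA1c points before baseline adjustment. That is enough to move the false-positive rate from 5% to between about 6% and 20%, and well short of the full 0.5 target. It is not shown that the data are missing, that an imbalance exists or that it favours the programme.

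**What to change.** - Check that date of diabetes diagnosis and glucose-lowering treatment as of randomisation (June 5th 2007) are recorded identically in both arms. Where they are not, add them to the additional case report form planned for the final examination, filled in from surgery records.
- Name diabetes duration and baseline HbA1c as covariates in the primary model.
- Enter treatment class only as it stood before randomisation. Treatment at inclusion is not safe as a covariate: inclusion ran from July 1st to October 31st, after allocation and during or after physician training, so it may already reflect the intervention, and adjusting for it could remove part of the programme's effect.
- Pre-specify a sensitivity analysis of the primary endpoint without recently diagnosed patients, at least without those diagnosed after June 5th 2007. These patients have no duration at randomisation, and their diagnosis may itself follow from the training.
- State what the preventive medication item covers.

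The cost is a short chart look-up, a few extra model terms and slightly fewer patients in the sensitivity analysis. The sample size is unchanged.

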### Endpoints

The primary endpoint of the trial will be the change in HbA1c from baseline to 12 months (final examination). Secondary outcomes will include a reduction in the amount of time spent in a hospital during the year of the study, a higher percentage of patients with guideline adherent diagnostic and therapeutic measures (i.e. eye examination, foot examination frequency) during the study, as well as improved control of cardiovascular risk and a higher EQ5-D-score in the intervention group at the end of the study.

The differences between the intervention group and the control group regarding primary and secondary endpoints will allow an estimate of the impact of the DMP on health economics.

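### The covariates listed for the HbA1c change model do not name baseline HbA1c, although it is collected and the plan relies on adjustment to correct for differential recruitment

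*Protocol article*

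**What the plan says.** The Statistical Analysis section states: "The primary efficacy analysis will be to compare the change in the HbA1c from baseline to 12 months in the intervention and control groups". Group differences are estimated "by using mixed models in SPSS 13.5 to allow for clustering". On covariates the commitment is general at first, "We will add all relevant baseline characteristics at patient level", and a bracket then names six: "age, sex, educational level, cardiovascular risk, clinical vascular disease, medication for primary and secondary prevention". Cluster-level characteristics may be added where applicable. Baseline HbA1c is not in the bracket, and no other section says that it enters the model.

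It is available. The Baseline-Examination section records "Fasting and postprandial blood glucose, HbA1c, cholesterol, triglycerides, HDL-cholesterol" at inclusion, together with weight and blood pressure.

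Two further statements bear on the point. The abstract says "Physicians are randomized before recruitment of patients with the districts of Salzburg as clusters of randomisation", so allocation is settled before any patient is enrolled. The Discussion concedes the consequence, "Thus physicians in the intervention group may recruit different patients than those in the control group", and offers multivariate adjustment as the way to overcome it.

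**The concern.** A change score does not remove a baseline difference between arms. Patients with a high HbA1c at inclusion tend to fall more over a year than those with a low one, whatever the treatment. If physicians already trained in the programme enrol worse-controlled patients, the unadjusted change favours the programme with no true effect. If they enrol better-controlled patients, it works against the programme. With six allocated units in three matched pairs (Randomisation section), chance imbalance is possible as well.

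The plan's safeguard against recruitment differences is covariate adjustment, yet the named list lacks the variable most directly tied to the primary outcome. At stake are a possible shift in the primary estimate and some avoidable loss of precision.

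**Working it through.** **Inputs from the section on data management and sample size:** SD of HbA1c change 2 points, target difference 0.5 points, 80% power, two-sided 0.05, intracluster correlation 0.05, average cluster size 20, dropout 20%.

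**Inputs the article does not give, so assumed:** correlation r between baseline and 12-month HbA1c (0.3, 0.5, 0.7), equal SD s at both visits, and a baseline difference d, intervention minus control (0.3 points as illustration).

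**1. The plan's own figure.** These inputs give 252 per arm. Then 252 × 1.95 = 491.4, rounded up to 492, and 492 / 0.8 = 615 per arm. The stated sample size reproduces exactly, so this is not an arithmetic point.

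**2. Bias of the change score.** If both arms regress to a common mean with slope r, the expected 12-month difference without a treatment effect is r·d. The expected difference in change is r·d − d = −(1−r)d.

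**3. Patient-level variance.** Var(change) = 2s²(1−r). Var(adjusted for baseline) = s²(1−r²). The ratio is (1+r)/2, so the adjusted residual SD is 2 × √((1+r)/2).

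| r | Shift for d = 0.3 | Share of 0.5 target | Variance ratio | Residual SD (2.0 unadjusted) | Power at 252 per arm, no clustering |
|---|---|---|---|---|---|
| 0.3 | 0.21 | 42% | 0.65 | 1.61 | 94% |
| 0.5 | 0.15 | 30% | 0.75 | 1.73 | 90% |
| 0.7 | 0.09 | 18% | 0.85 | 1.84 | 86% |

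The shift is linear in d. For d = 0.1 it is 0.07, 0.05 and 0.03; for d = 0.5 it is 0.35, 0.25 and 0.15.

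**4. Simulation check** (2000 runs, 252 per arm, no true effect, no clustering, d = 0.3, regression to a common mean). The mean change-score difference was −0.147 at r = 0.5 and −0.085 at r = 0.7. With baseline HbA1c in the model it was 0.004 and 0.003. The empirical standard error fell from 0.180 to 0.158 and from 0.182 to 0.167.

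**5. What clustering leaves of the precision gain.** The ratio in step 3 applies to the patient-level part of the variance only. With the article's own figures that part is (1 − 0.05) / 1.95 = 0.95 / 1.95 = 49% of the total. If the between-cluster part were unchanged by adjustment, the reduction would be 0.49 × 35% = 17% at r = 0.3, falling to 0.49 × 15% = 7% at r = 0.7. If a correlation of 0.05 applied instead at the level of the six allocated units (1494 / 6 = 249 patients each), the patient-level share would be 0.95 / (1 + 248 × 0.05) = 0.95 / 13.4 = 7%, and the gain about 1% to 2.5%.

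**6. Choice of outcome.** With baseline in the model, change = 12-month value − baseline. Switching between change and the 12-month value therefore alters only the baseline coefficient, by exactly 1. The treatment estimate is identical.

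**The case against.** **The general wording may already cover it.** The bracket follows a promise to include every relevant baseline characteristic, and the Discussion promises adjustment for recruitment differences. The article also uses brackets elsewhere for what look like examples. A reader might infer that the plan excludes baseline HbA1c; the text does not support that. What stands is that it is not named: the bracket carries no sign of being illustrative, so the primary model can be read two ways. An article may leave detail to a fuller plan, but this one chose to print a list.

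**The size is hypothetical.** A reader might infer that the trial's estimate is biased. The article gives no baseline HbA1c by arm and no r, and the Current status section says baseline data were still being processed. The unequal recruitment reported there (654 against 840) shows nothing about HbA1c levels. This objection stands, so the figures are conditional.

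**Adjustment is not free of risk.** If the arms differ stably in HbA1c level, the change score is unbiased (d − d = 0), while the adjusted comparison gives d − r·d = d(1−r): the same size as in the table, with the opposite sign. The simulation builds in a common mean and cannot settle which case applies. This stands, and it is why the fix keeps both analyses.

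**Secondary outcomes.** A reader might infer that these go wholly unadjusted for their baselines. The Endpoints section names control of cardiovascular risk as an outcome, and cardiovascular risk is among the listed covariates, so its baseline counterpart is covered at least at composite level. What remains open is whether that covariate supplies the baseline value of each individual measure.

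**Conclusion.** The point holds as an under-specified primary model: baseline HbA1c is collected, is a strong predictor of the outcome, is the covariate the plan's own remedy most needs, and is not named. If only the listed covariates are used, an assumed 0.3-point imbalance shifts the comparison by 0.09 to 0.21 points, or 18% to 42% of the target. That rests on assumed r of 0.7 to 0.3, equal SDs at both visits and regression to a common mean. Patient-level residual variance would be 15% to 35% lower with adjustment. The gain in the treatment estimate itself is smaller, and could be slight if between-district variance dominates. The documents do not show that an imbalance exists or in which direction it would run.

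**What to change.** Name baseline HbA1c as a mandatory covariate in the primary mixed model, with either change or 12-month HbA1c as outcome. Keep the analysis without it as a prespecified sensitivity analysis, and say that a marked disagreement between the two will be read in the light of baseline HbA1c by arm and district.

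For continuous cardiovascular risk-factor outcomes measured at inclusion (blood pressure, lipids, weight), use the baseline value of the same measure wherever the listed cardiovascular-risk covariate does not already supply it.

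The cost is small: one covariate already collected and one extra analysis, with no change to sample size or conduct. It should be fixed before the 12-month data are examined.
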